In 2006, the Center Brittany region had a population of 103,674 people. There is an excess of cardiovascular deaths in the region, with a specific mortality index of 113 CVD-related deaths in the region compared to 100 in the general French population. The Interheart cardiovascular risk is divided into terciles for equal populations, which suggests that one-third of people screened have a moderate or orange CVDR. A total of 7,350 people would have to be screened to reach the number of participants to be included of 2,400 in all the arms, an estimate that includes those lost to follow-up during the intervention. Based on other general population screenings, it can be estimated that 30% of general population contacts refuse to undergo screening or to be included in the study. This brings the total number of contacts per screener to 9555, assuming 250 screeners, i.e. an average of 36.75 contacts per screener. The capacity to recruit screeners is high because of the creation of the preventative health service for medical and paramedical students and the service is consistent with the SPICES project (90 medical students in Brest, 90 nursing students in Pontivy, 30 physiotherapy students in Brest). Other training courses, such as preparatory classes in nursing, have shown an interest in the project because of a similar fit (40 students in a preparatory class in Gourin). Presentations to associations in the Centre Bretagne region offer further opportunities.

40 community champions are needed to perform the behavioral change sessions. Some fifteen contacts from associations in the area have shown an interest in this role, as have students from the citizen's prevention university. The research team benefits from the social expertise of the chair of the region's health commission and a regional coordinator, as well as the support of the COB regional council. The research team has expertise in behaviour change and communication techniques (training leading to qualifications in therapeutic education).

1. Final report and publishing rules

All actors who have contributed substantially in study design, data collection, data analysis and interpretation, manuscript preparation and critical revising, and in final manuscript version approval, will be affiliated as authors. The sponsor and funders will be acknowledged in the published manuscript.

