- Validation of a clinically effective and profitable prevention model
  - 1. Risks
       1. Individual risk

The risks to which the participant is exposed are, on one hand, the risk of over-diagnosis linked to the screening strategy using the Non Laboratory Interheart risk score and, on the other hand, the risk of over-treatment in people detected as having a high CVDR according to the Non Laboratory Interheart risk score.

Finally, there are psychological risks, mainly increased anxiety and reduced self-confidence. There are no painful or physically demanding examinations.

- - - 1. Collective risk

No collective risk is expected.

- - 1. Benefit/risk balance

In terms of the expected benefits and the risks to individuals, the benefit/risk balance is in favour of the intervention.

- 1. Declaration that the research will be conducted in accordance with the protocol, good clinical practice and the legislative and current regulatory provisions

The sponsor and the investigator also undertake that this research will be conducted :

- in accordance with the protocol,

- in accordance with current French and international good clinical practice,

- in accordance with the French and internationanl laws and regulations.

1. Objectives
   1. Main objective

To evaluate the effectiveness of a community-led behaviour change programme and brief intervention for people at moderate cardiovascular risk (according to the Non Laboratory Interheart risk score) on CVDR reduction versus brief intervention.

- 1. Secondary objectives

Identify and assess the obstacles and barriers for carrying out the intervention:

- During the screening phase
- During the intervention phase (RCT)
- For those involved in screening and intervention
- For participants

1. Study design and outcomes
   1. Qualification of research and investigators

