6.2.3.1. Study follow-up for participants

In addition to contacts at 6, 12, 18 and 24 months, the psychological risks associated with the intervention will be collected with a specific question: "Did the participants experience any psychological effects associated with the research?

- 1. Study process

Each intervention group will hold an initial research action meeting between people with moderate CVDR and community leaders.

The aim of this meeting is to map external resources in the COB region that help the improvement of modifiable risk factors (sports associations, for example).

Each group will then meet regularly, face-to-face and/or remotely (by telephone or videoconference), under the aegis of the community champions, to work on the changes in each participant's risk factors. The one-hour sessions will be scheduled every fortnight for 2 months, then every month for 2 months, then every 3 months until the end of the study (13 sessions). These sessions will be behaviour change sessions, focusing on goal setting, action planning and problem solving. The community champions will lead these sessions and use motivational interviewing techniques.

Community champions will first take part in a 2-day training course with national experts (run in France by UNAFORMEC, a certified training association).

The community champions will be compensated for their time on a lump-sum basis. This is consistent with the interventions proposed by the other partners in the SPICES consortium.

At the same time as these sessions, the people in the intervention group will be contacted individually (face-to-face or remotely by telephone or videoconference) by the research team. The aim of this contact will be to help them make lifestyle changes to improve primary cardiovascular prevention.

The volunteer community champions will be supported by family medecine interns under the supervision of the research team. These family medecine interns of the Faculty of Brest will be working on this project as part of their mandatory master thesis. They will support the community champions, offering them logistical assistance (organising face-to-face or remote meetings), help in running their meetings and assisting the members of their groups to change their lifestyles in favour of better cardiovascular prevention.

At 6, 12, 18 and 24 months, various criteria will be measured by the research team:

- Quantitative implementation assessment criteria :

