- Qualitative assessment of non-participants using semi-structured individual interviews. Non-participants are defined as people who have been screened but have been lost to follow-up or have disappeared during the intervention. A purposive sampling of non-participants will be carried out. It will be based in particular on age and the geographical location of the sessions. Data collection will continue until the theoretical saturation point is reached. Data analysis will use a thematic analysis. Two researchers will analyse the data blindly and then collate the analyses.
  1. Identifying the data collected in the observation notebook

Data collected will include demographics, history, weight, height, BMI of participants, responses to Interheart questionnaires, Whoqol brief quality of life, IPAQ short physical activity, DASH-Q diet, self-reported level of smoking and self-reported level of alcohol consumption.

Demographics :

- Age
- Tobacco consumption according to Interheart (never smoked, former smoker, smoker of 1 to 5 cigarettes a day, 6 to 10 cigarettes a day, 11 to 15 cigarettes a day, 16 to 20 cigarettes a day, more than 20 cigarettes a day)
- Passive smoking, formulated according to Interheart
- Diet according to Interheart criteria (5 questions) and DASH-Q criteria (11 questions)
- Quality of life using the short Whoqol scale, 26 items exploring 4 areas: physical health, mental health, social relationships and the environment.
- Physical activity based on Interheart and IPAQ-short data (7 questions)

History

Family history: history of heart attack in fathers or mothers

Personal history: existence of type 2 diabetes, arterial hypertension, etc.

Clinical data :

- Weight, height and BMI of intervention participants
- Waist to hip ratio measured with a tape measure according to Interheart recommendations
- Professional and personal stress formulated according to Interheart
- Depression and related syndromes as formulated by Interheart
- Specific risk assessment question: did the participant experience any psychological effects related to the research?
  1. Expected duration of participation and description of duration of all trial periods, including follow-up, if applicable

The duration of screening and inclusion in the intervention and control groups will be one year.

The intervention will last two years.

The total duration of the intervention (screening + intervention) will be three years.

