Participants will participate in the study for three years.

- 1. Support for research

There is no standard management of primary prevention patients in the community. The specific research management was created on the basis of the results of a structured review of the literature on the best current recommendations for good practice in primary care, adressing an adapted diet, adapted physical activity, reduction or cessation of smoking and alcohol, and weight loss.

- 1. Withdrawals
     1. Withdrawal of participants

Participants may withdraw their consent and ask to leave the study at any time and for any reason. In the event of premature withdrawal, the investigator must document the reasons as fully as possible.

The investigator may temporarily or permanently discontinue a participant’s participation in the study for any reason that is in the best interests of the participant, particularly in the case of serious adverse events.

If a participant is lost to follow-up, the investigator will make every effort to contact the person again*.*

- - 1. Total or partial arrest of the study

Unforeseen events or new information relating to the research, in the light of which the objectives of the study are unlikely to be achieved, may lead the sponsor to interrupt the study prematurely.

The CHRU de Brest reserves the right to discontinue the study at any time if the inclusion objectives are not met.

1. Safety assessment

As part of this study, investigators will report research-related adverse events occurring during the participation of recruited patients via the electronic CRF. The sponsor will receive an e-mail alert whenever an AE is entered into this CRF. This information will be used to create a register which will be used to draw up the final study report.

In accordance with the Public Health Code, new facts (defined in 12° of article R1123-46) will be reported to the CPP.

1. Statistics

Responsible for analysis: UGD - Brest Clinical Research and Innovation Delegation - CHRU de Brest - [name]

All analyses were carried out using SAS and R software.

Analyses will be carried out with an alpha risk of 0.05

- 1. Description of planned statistical methods,

The general principles of the analysis are :

- The analysis will be conducted on "intention to treat".
- There is no intermediate analysis because there is no biomedical risk associated with the research.

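### The one dedicated question on psychological risk has no direction, so a raw count of yes answers cannot be read as harm

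*Protocol*

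**What the plan says.** Section 2.3.2.1 (Individual risk) lists over-diagnosis, over-treatment of people found to be at high risk, and then psychological harm: "there are psychological risks, mainly increased anxiety and reduced self-confidence". Both examples are adverse.

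Section 6.2.3.1 (Study follow-up for participants) says that the psychological risks of the intervention are to be collected with a specific question, and gives it: "Did the participants experience any psychological effects associated with the research". Section 6.4 carries the item in its list of clinical data: "Specific risk assessment question: did the participant experience any psychological effects related to the research". Neither place adds a direction, a severity, a free-text follow-up or a rule for a favourable answer.

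Three other sources bear on psychological state:

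- Section 7 (Safety assessment): "investigators will report research-related adverse events occurring during the participation of recruited patients via the electronic CRF".
- Section 6.4, on the WHOQOL brief scale: "26 items exploring 4 areas: physical health, mental health, social relationships and the environment". Section 6.2 has it measured in both arms at baseline and at 6, 12, 18 and 24 months.
- Section 6.4, among the Interheart items: "Depression and related syndromes as formulated by Interheart", together with work and personal stress.

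**The concern.** The risk is defined by direction and the item meant to measure it has none. The intervention consists of group sessions using motivational interviewing (13 are planned) plus individual contacts with the research team, over two years. Feeling supported or more confident is a plausible result, and is itself a psychological effect linked to the research. Followed as worded, the question lets that answer and a report of new anxiety enter the same box.

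At stake is how far this item can inform the benefit/risk statement in section 2.3.3. Section 2.3.2.1 notes that no examination is painful or physically demanding, so psychological harm is one of only three individual risks named. If direction is not recorded when the question is asked, no later analysis can recover it.

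**Working it through.** **Step 1. Set the texts side by side.**

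| Place | Role | Direction |
|---|---|---|
| 2.3.2.1 | Defines the risk | Adverse (more anxiety, less self-confidence) |
| 6.2.3.1 | Fixes the question that collects the risk | None |
| 6.4 | Lists the same item, labelled as risk assessment | Label implies adverse; wording has none |

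A participant made anxious by the risk score is a yes. A participant made more confident by the sessions can also be a yes. A participant with no effect is a no. The item does not separate the first two.

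**Step 2. Ask whether another listed source separates them.** Adverse-event reporting (section 7) is adverse by definition and tied to the research, so it partly does. However, it relies on what investigators report and is not a standard question on anxiety or self-confidence put to every participant. WHOQOL mental health and the Interheart stress and depression items are not attributed to the research. WHOQOL is also a secondary efficacy endpoint. The cover is therefore partial.

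**Step 3. Look for a figure to reproduce.** There is none. The protocol gives no psychological-harm rate, no rule that yes means harm and no planned comparison of harm between arms. The size below is an illustration from assumed inputs.

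**Step 4. Illustrate.** Let h be the true harm rate, equal in both arms, and b the rate of favourable effects reported, independent of harm. If every yes were counted as harm:

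- P(yes) = 1 − (1 − h)(1 − b)
- spurious difference between arms = (1 − h)(b_int − b_ctl)

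With h = 5%:

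| b, control | b, intervention | yes, control | yes, intervention | spurious difference |
|---|---|---|---|---|
| 0% | 0% | 5.0% | 5.0% | 0 |
| 2% | 5% | 6.9% | 9.8% | 0.95 × 0.03 = 2.8 points |
| 2% | 10% | 6.9% | 14.5% | 0.95 × 0.08 = 7.6 points |
| 5% | 20% | 9.8% | 24.0% | 0.95 × 0.15 = 14.2 points |

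In the third row, 0.05/0.145 = 34% of yes answers in the intervention arm include a harm. With h from 2% to 10% and the same favourable rates, the spurious difference runs from 0 to 14.7 points (0.98 × 0.15). It depends mainly on how far favourable reports differ between arms, for which the documents give no value.

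**The case against.** The strongest reply is that nothing in the protocol says a yes will be counted as harm. Section 8 plans tests for the primary endpoint and six secondary endpoints, and this item is not among them. Answer format and coding may sit in the eCRF or the analysis plan, which are not shown. Both versions of the question are in the third person, so they may be prompts for an interviewer, who would take the adverse meaning from the label. The text also appears to be an English version of a French protocol, and the wording in use may differ.

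Much of this stands, and it rules out three stronger readings that a reader might infer:

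- *That this is the trial's only source on psychological harm.* It is the only dedicated question; section 7 also collects research-related adverse events.
- *That the recorded harm rate is wrong, or that a comparison of arms will falsely show excess harm.* No such rate or comparison is defined, so a false-positive rate would describe a test that nobody has planned.
- *That the intervention arm is worst affected.* This is a reasonable inference from its extra contact, but it is not documented. The question sits under the intervention-group heading and refers to risks of the intervention, so it is unclear whether controls are asked it at all. If they are not, there is no between-arm contrast to distort, though the mixing of harm and benefit within the intervention arm remains.

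The reply does not remove the mismatch. The protocol itself fixes the question's wording, and that wording is broader than the risk it is meant to collect.

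**Conclusion.** The point holds as a limited one on safety measurement. The dedicated question admits favourable effects although the risk it serves is defined as adverse, so a raw yes count cannot be read as harm. The distortion cannot be sized from the documents. It is zero if no favourable effects are reported, and reaches 14.7 points between arms under the most unequal rates assumed here. Those figures require that every yes is counted as harm, that both arms are asked, that true harm is equal in the two arms, and that favourable effects are reported at the assumed rates. The primary endpoint, the sample size and the testing hierarchy are unaffected.

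**What to change.** Reword the item in sections 6.2.3.1 and 6.4 so that it asks about negative effects. For example: *Have you had any unpleasant psychological effect that you link to the study, such as feeling more anxious or less sure of yourself? (no / yes: which)*. Alternatively, keep the broad question and record the direction of each effect. If favourable effects are of interest, give them a separate box.

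State that both arms are asked, at the same contacts.

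For answers already collected under the present wording, do not tabulate the raw yes count as harm. Where free text exists, have it classified as negative or positive by someone who does not know the arm.

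The cost is one changed eCRF question and a short protocol amendment, with no added visits or participants if controls are asked at the contacts they already have. The downside is small: answers before and after the change are not directly comparable and should be reported separately.

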6.2.3. The Intervention group

6.2.3.1 Inclusion

In the intervention group, people with moderate CVDR will receive brief advice followed by a multi-behavioural intervention adapted to local resources.

The intervention was defined on the basis of a systematic review of international and national good practice recommendations for cardiovascular prevention.

The diet will follow the Dash Diet recommendations.

The reduction of tobacco and alcohol consumption will be proposed.

Increased physical activity will be recommended as a combination of aerobic and resistance activity.

There is no provision for compensation for people included in the intervention group. A review of the literature shows that financial incentives are not effective when used alone. On the other hand, when they are combined with a multimodal intervention, their effect is moderate and ceases when the funding is stopped (21). The aim of our project is to ensure that the intervention lasts beyond the end of the project. Secondly, financial incentives belong to a different category of the behaviour change taxonomy from that currently adopted by the SPICES consortium (including goal setting, problem solving and action planning) (22). This incentive would change the method of our intervention and create a divergence from the projects of the other members of the SPICES consortium.

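### Adverse event reporting is limited to events judged research-related, so all-cause harms are not systematically captured and any comparison of the safety register between arms is open to bias

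*Protocol*

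**What the plan says.** Section 7 (Safety assessment) sets the collection rule: "investigators will report research-related adverse events occurring during the participation of recruited patients via the electronic CRF". On the use of these entries it adds: "This information will be used to create a register which will be used to draw up the final study report". The only other channel in that section is regulatory: "new facts (defined in 12° of article R1123-46) will be reported to the CPP".

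Section 6.4 lists the contents of the observation notebook. It opens "Data collected will include demographics, history, weight, height, BMI of participants, responses to Interheart questionnaires" and goes on to the questionnaires, family and personal history, and clinical measurements. Its single harm item asks "did the participant experience any psychological effects related to the research". Death, cardiovascular event, hospital admission and injury are not named.

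The arms differ in what they receive. Controls get brief advice (6.2.2). The intervention arm gets the same advice and then a multi-behavioural programme, in which "Increased physical activity will be recommended as a combination of aerobic and resistance activity" (6.2.3). Section 6.3 schedules 13 group sessions and individual contacts by the research team for that arm. Both arms are interviewed at baseline and at 6, 12, 18 and 24 months (6.2).

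Section 6.7 asks for the reasons for premature withdrawal to be documented and names serious adverse events as a ground for ending participation. Neither provision depends on relatedness.

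**The concern.** Relatedness is used here as the condition for entering an event, when it could be an attribute recorded on each event. An infarction, fracture or death that nobody attributes to the research has no required place in the record, in a trial of cardiovascular prevention that follows people for two years. This is a rule about data collection, so an analysis plan cannot repair it later.

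The rule may also work differently in the two arms. An injury during recommended exercise has an obvious research activity to be linked to, while the same injury in a control usually does not. The protocol describes no blinding of the person who makes that link. Family practice interns collect data (4.1), and interns also help to run the group sessions (6.3). A tabulation of the register by arm could therefore show an excess in the intervention arm that reflects attribution and contact alone.

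At stake is the support for two statements in the protocol: the favourable benefit/risk balance (2.3.3) and the absence of biomedical risk, given as the reason for having no interim analysis (8.1).

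**Working it through.** **1. The text.** Three questions settle what is collected.
- Does any section require all adverse events, or all serious ones, whatever the cause? None does. Section 7 requires research-related events only.
- Does another item solicit harms without the filter? No. The psychological-effects item carries the same restriction. It appears in 6.4 without an arm restriction, but in 6.2.3.1 under the intervention-group heading, so it is unclear whether controls are asked.
- Is there any route for unrelated events? Yes, an incidental one: withdrawal reasons and discontinuation for serious events (6.7). It reaches only participants who leave.

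**2. The plan's own numbers.** The protocol states no safety figure. Its sample size reproduces: an effect size of 0.20, two-sided alpha of 0.05 and 80% power give 393.4 per arm by the t-test calculation, hence 394. Then 2 × 394 / (1 − 0.20) = 985.

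**3. How many events could be involved (assumed rates).** Take 0.5% to 1.5% per year for death or a cardiovascular event; the protocol gives no rate.
- Full follow-up: 985 × 2 = 1,970 person-years, giving 1,970 × 0.005 = 9.9 to 1,970 × 0.015 = 29.6 events.
- If the planned 20% loss contributed no time: 788 × 2 = 1,576 person-years, giving 7.9 to 23.6 events.

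**4. What the filter can do to a comparison (assumed attribution).** Let N = 492 per arm (985 / 2, rounded down), r the true 24-month risk of any event, equal in both arms, and q the share judged related. Register count = N × r × q, so the ratio between arms is q(intervention) / q(control), whatever r is.

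| r | True events per arm | q 10% v 10% | q 20% v 10% | q 20% v 2% |
|---|---|---|---|---|
| 2% | 9.8 | 1.0 v 1.0 | 2.0 v 1.0 | 2.0 v 0.2 |
| 5% | 24.6 | 2.5 v 2.5 | 4.9 v 2.5 | 4.9 v 0.5 |
| 10% | 49.2 | 4.9 v 4.9 | 9.8 v 4.9 | 9.8 v 1.0 |

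The apparent ratio runs from 1 to 10 although the arms do not differ. The higher values of r allow for injuries and admissions as well as cardiovascular events.

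**5. What full recording could show.** The rates in step 3 are 24-month risks of 1% to 3%. Power to detect a halving, with 492 per arm, is about Φ(|p1 − p0| / SE − 1.96), where SE = √{[p1(1 − p1) + p0(1 − p0)] / 492}.
- 1% v 0.5%: SE = 0.0055, so Φ(0.909 − 1.96) = 15%.
- 3% v 1.5%: SE = 0.0094, so Φ(1.588 − 1.96) = 36%.

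**The case against.** The strongest reply is that this is a minimal-risk study without health products (4.1), safety is neither an objective nor an endpoint, and no comparison of harms between arms is promised. That stands as far as it goes: the plan breaks no promise, and whether its legal category permits relatedness-limited reporting cannot be judged from the protocol. Permission would not remove the bias, however, and section 7 does commit the register to the final report.

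Four further replies limit the point.
- **Unrelated events can be recorded.** Section 6.7 documents withdrawal reasons and calls for renewed contact with people lost to follow-up. A reader might infer that unrelated events go wholly unrecorded, or that most do. The text supports only that they are not systematically captured.
- **The 6.4 list is not exhaustive.** It is introduced as an inclusive list and omits even the adverse event entry that section 7 places in the eCRF. Its silence does not prove that no such field exists. The rule in section 7 does not depend on it.
- **Controls can have research-related harms.** Over-diagnosis and anxiety (2.3.2.1) can follow from the screening that both arms undergo. The register need not hold intervention-arm events only.
- **Events will be few.** Step 5 of the working bears this out. Full recording would improve the description of harms but would probably not detect a difference.

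Three stronger readings are tempting and fail.
- One is that over-treatment among randomised participants would be missed. The protocol names "the risk of over-treatment in people detected as having a high CVDR according to the Non Laboratory Interheart risk score", and people scoring above 15 are excluded from randomisation.
- Another counts the 13 sessions as reporting occasions and sets 17 against 4. No section makes a session a point of event collection, section 7 gives reporting to investigators, and full attendance is not assured. Contact is unequal, but that ratio is not established.
- The third objects that participants who have an event stay in the 24-month comparison. Intention to treat implies exactly that.

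**Conclusion.** The point holds as a weakness in data collection. Reporting is conditional on a relatedness judgement for which no blinding is described. All-cause harms are not systematically captured, and a comparison of the register between arms is open to bias, because the intervention arm has more research activity and more contacts. The text establishes the mechanism but not its size. On assumed attribution shares the apparent ratio between identical arms ranges from 1 to 10, and on assumed rates about 8 to 30 deaths or cardiovascular events are at issue. Neither range comes from the protocol. The primary endpoint comparison is not shown to be affected. The change is worth making because it is cheap and cannot be made after the data are collected.

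**What to change.** Amend sections 7 and 6.4 as follows.
- Add a short fixed checklist, asked identically in both arms at the existing 6, 12, 18 and 24 month contacts, whatever the cause: death, hospital admission, cardiovascular event, injury, new cardiovascular or metabolic diagnosis, new cardiovascular drug.
- Record relatedness as a separate field on each event, not as the condition for entry.
- State that the psychological-effects question is asked in both arms.
- Base any description of harms by arm on these visit-collected events, and list separately those heard of at sessions or individual contacts.

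The cost is a protocol amendment, about six CRF fields, a few more minutes per visit and more eCRF alerts to the sponsor. With so few events expected, the protocol should say that the comparison is descriptive. The change concerns data collection only.
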